## Abstract

The GAITFAST study (gait recovery in patients after acute ischemic stroke) aims to compare the effects of treadmill-based robot-assisted gait training (RTGT) and therapist-assisted treadmill gait training (TTGT) added to conventional physical therapy in first-ever ischemic stroke patients. GAITFAST (Clinicaltrials.gov identifier: NCT04824482) was designed as a single-blind single-center prospective randomized clinical trial with two parallel groups and a primary endpoint of gait speed recovery up to 6 months after ischemic stroke. A total of 120 eligible and enrolled participants will be randomly allocated (1:1) in TTGT or RTGT. All enrolled patients will undergo a 2-week intensive inpatient rehabilitation including TTGT or RTGT followed by four clinical assessments (at the beginning of inpatient rehabilitation 8–15 days after stroke onset, after 2 weeks, and 3 and 6 months after the first assessment). Every clinical assessment will include the assessment of gait speed and walking dependency, fMRI activation measures, neurological and sensorimotor impairments, and gait biomechanics. In a random selection (1:2) of the 120 enrolled patients, multimodal magnetic resonance imaging (MRI) data will be acquired and analyzed. This study will provide insight into the mechanisms behind poststroke gait behavioral changes resulting from intensive rehabilitation including assisted gait training (RTGT or TTGT) in early subacute IS patients.

## 1. Introduction

After ischemic stroke (IS), the majority of people have some walking disabilities. Approximately 30% of IS patients are unable to walk without assistance six months after a stroke [1], and more than 60% of individuals who achieve independent ambulation after IS still walk at speeds insufficient to function effectively in the community [2]. Walking is one of the most important activities of daily living (ADL), and restoring gait function has become a critical goal of poststroke rehabilitation [2,3].

Early neurorehabilitation interventions seem to be critical to enhance neural plasticity and brain repair processes and to potentiate physiological motor behavioral restitution (i.e., restoring the physiological movement pattern) rather than mere compensation (adaptive mechanisms to utilize the residual capacity to accomplish a motor task) [3,4]. Functional brain imaging provides the possibility to describe neuroplastic brain adaptations related to motor recovery [5] and rehabilitation [6].

Current neurorehabilitation approaches mostly focus on task-specific training and intensive and repetitive exercise [7,8,9,10,11] with increases in both the therapy dosage and intensity [3,11]. Additional (add-on) physical rehabilitation, as compared to usual care or a control intervention, demonstrated the potential to further improve motor function, standing balance, or walking speed [11]. As the vast majority of poststroke patients experience some recovery, mostly occurring in the first weeks after stroke [4,12,13], the optimal time window to begin rehabilitation seems to be the early subacute stage (within the first weeks after stroke onset [14]).

Gait training is fundamental to promote poststroke gait recovery. The character of gait training should always reflect the individual patient’s walking ability [15] and might be realized with the assistance of a therapist or a robot, on the ground or on the treadmill, and with or without body weight support [10]. Conventional gait training also includes therapist-assisted gait training on a treadmill (TTGT) [16], which represents a repetitive task-specific activity with the possibility of a high number of repetitions produced through taken steps [17]. TTGT provides the opportunity to optimize the walking pattern with appropriate therapeutic handling. Treadmill gait training, even without a therapist’s assistance, has mostly been shown to improve walking abilities in subjects after stroke in the chronic phase [17,18,19]. Using treadmill gait training allows increases in the intensity of practice if overground walking is limited [19]. As the intensive treadmill gait training is stopped in chronic stroke survivors, the effect of this training declines [17]. It remains unclear whether intensive task-specific training has the potential to facilitate motor recovery through the restoration of physiological movement patterns or if it just improves physical fitness with a persisting compensatory walking pattern in chronic stroke patients.

Currently, robot-assisted gait training represents a rapidly advancing approach in neurorehabilitation [15]. Many patients early after stroke have a decreased ability to correctly produce volitional movements, and robot- or therapist-assisted gait training reduces unwanted compensations. Gait training should be, especially in the early subacute stage, continuous and repetitive. During robot-assisted gait training, an exoskeleton enables the application of a guidance force provided by the robotic orthosis to induce walking-like motion. Robot-assisted treadmill gait training (RTGT) systems are commonly used in combination with body weight support [15], allowing patients to engage in the repeated practice of complex gait patterns at near-normal speed over a longer period with less energy consumption and reduced effort given by the therapist [14,16]. Compared to treadmill gait training, RTGT may provide a longer training duration, the production of a greater number of step repetitions, more reproducible symmetrical gait patterns, and a reduction in the energy expenditure imposed upon the patient [15,16,20]. Some recent studies advocated for the use of RTGT versus treadmill or conventional gait training [21,22] and reported that robot-assisted gait training with concomitant physical therapy is more effective for gait recovery in stroke patients than physiotherapy alone [11,14,16,22,23,24]. Furthermore, Kim et al. [10] stated that RTGT, in comparison to bodyweight-supported treadmill training in hemiparetic poststroke participants, leads not just to improved functional clinical outcomes but also to increased cortical activity in the affected hemisphere, which may suggest that RTGT potentiates locomotor-task-related neuroplasticity [9,11].

To our knowledge, to date there is no study that has compared these two types of assisted gait training. Since they both facilitate a normal gait pattern, both are used in the clinical practice, and each possesses different strengths and limitations. Furthermore, limited evidence of the factors predicting the success of gait recovery after stroke exists, and a better understanding of the process of gait recovery early after IS in the context of intensive assisted gait rehabilitation remains the key research objective. The protocol of our study presents the first head-to-head comparison of RTGT versus TTGT, both added to conventional rehabilitation in the early subacute stage, evaluating their effects on the course of gait recovery for up to 6 months after a first-ever ischemic stroke. Our study reflects the current need for robust randomized clinical trials with clearly defined dosages and characters of rehabilitative interventions that are reliably evaluated using relevant clinical data, biomechanical parameters, and functional brain imaging data for further understanding the mechanisms behind poststroke gait behavioral changes and to define possible predictors of gait recovery, i.e., to identify brain structures with possible impacts on gait recovery using functional magnetic resonance imaging (fMRI), diffusion-weighted imaging (DWI), and surface-based morphometry up to 6 months after a first-ever ischemic stroke. The results of the proposed study will support decision making in poststroke rehabilitation regarding the timing, type, and setting of the interventions that are provided and facilitate realistic goal setting.

## 2. Materials and Methods

### 2.1. Study Design

The GAITFAST study (gait recovery in patients after acute ischemic stroke) was designed as an investigator-initiated, academic, single-blind, single-center, prospective, randomized clinical trial with two parallel groups and a primary endpoint of gait speed recovery up to 6 months after ischemic stroke. The protocol of the proposed GAITFAST trial is registered on ClinicalTrials.gov with identifier NCT04824482. The trial design follows the Recommendations for Interventional Trials (SPIRIT), the TIDieR checklist was used in conjunction with the SPIRIT. This study will be performed at the University Hospital Olomouc, Czech Republic. All participants will be enrolled at the Comprehensive Stroke Centre, and the neurorehabilitation interventions, including assisted gait training (RTGT or TTGT), will be performed at the Department of Rehabilitation.

### 2.2. Selection of Subjects

#### 2.2.1. Participants and Eligibility Criteria

The study population will consist of patients after first-ever IS who will be enrolled within 5–10 days after stroke onset at the Comprehensive Stroke Centre at the University Hospital Olomouc according to the following inclusion criteria: (1) first episode of unilateral ischemic stroke is detected on magnetic resonance imaging (MRI), resulting in walking deficits; (2) NIHSS score of 1–12 points at the time of enrolment; (3) lower limb movement impairment, with a score of at least 1 point on the NIH Stroke Scale (NIHSS) at the time of enrolment; (4) dependency in walking according to the Functional Ambulatory Category (FAC), with a score in the interval <1,3> (supervision or assistance, or both, must be given when walking) at the time of enrolment; and (5) age between 18 and 80 years. The exclusion criteria will include: (1) a previous history of any stroke, either ischemic or hemorrhagic; (2) other diseases modifying or limiting walking ability, currently receiving rehabilitation, or participation in another study; (3) significant or symptomatic ischemic heart disease; (4) significant or symptomatic peripheral arterial disease; (5) obesity (BMI ≥ 40) or weight higher than 135 kg (the weight limit for the robot-assisted gait training); (6) sensory aphasia with the inability to understand (confirmed by a certified speech therapist); (7) moderate or severe depression present at the time of enrolment assessed using the Beck scale, with a score above 10; (8) known cognitive impairment; (9) previous disability or dependence in daily activities assessed using the modified Rankin Scale, with a score of ≥3; (10) currently receiving dialysis; (11) diagnosed and/or receiving treatment for cancer; and (12) the presence of other orthopedic or neurological conditions affecting the lower extremities. Standard exclusion criteria for MRI examination will also apply.

#### 2.2.2. Screening and Recruitment

The screening of eligible participants with acute IS and their randomization for the GAITFAST trial will be performed by a certified neurologist at the Comprehensive Stroke Centre (University Hospital Olomouc). The neurologist will provide an overview of the study and determine initial interest in participation. All the potential risks and benefits related to study participation will be discussed with the participants. Potential participants will be informed that participating in the study is completely voluntary and that they may discontinue participation at any time. For individuals who express interest, the neurologist will determine initial eligibility and answer any participant questions. For individuals who agree to participate in this study and provide consent, the neurologist will perform screening procedures to confirm that the patient meets the eligibility criteria. By signing the informed consent, the participants will provide permission for the study investigators to obtain, collect, and analyze relevant data and to share them anonymously with the other members of the research team as well as to present or publish them anonymously at scientific conferences or in scientific journals. Regular screening of the study eligibility of all admitted patients with IS at the Comprehensive Stroke Centre by neurologists and physiotherapists (study investigators) will be performed every 2–3 days. Enough time will be given for the discussion with each eligible patient on his/her participation in the study, the study flow-chart, the importance of study follow-up, and informed consent.

### 2.3. Interventional Methods

#### Interventions

Enrolled participants will be randomly allocated into two groups before the start of the intensive rehabilitation at the Department of Rehabilitation at the University Hospital Olomouc, Czech Republic

Robot-assisted treadmill gait training (RTGT) is locomotor training guided by a robotic device Lokomat (Hocoma, Volketswil, Switzerland) on a treadmill according to a preprogrammed gait pattern with a robot-driven exoskeleton orthosis. The process of gait training is automated and controlled by a computer. The parameters of RTGT, such as guidance force or gait speed, are adaptively adjusted with respect to the patient’s actual walking abilities by a trained physiotherapist with at least 2 years of clinical experience on the Lokomat. Moreover, the dynamic body weight support system within this type of therapy is adjustable to the actual patient’s body-weight-bearing tolerance. RTGT is always realized under the supervision of a physiotherapist.

Therapist-assisted treadmill gait training (TTGT) is locomotor training via the repetitive execution of walking movements that are manually guided by a physiotherapist during treadmill gait training. Body weight support might be provided to patients during this type of gait training, if needed. Body weight support and gait speed are also adaptively adjusted with respect to the patient’s actual walking abilities as is the assistance, which is manually provided by physiotherapists with at least 4 years of clinical neurorehabilitation practice with poststroke patients. TTGT still represents a comparable type of training to RTGT, where each step might be adaptively corrected by the physiotherapist. However, the symmetrical stereotypical gait pattern might only be achieved in RTGT.

Assisted gait training (RTGT or TTGT) is performed five times per week, with durations of up to 30 min [23] for two weeks as an add-on therapy to conventional physical therapy. Adherence to the therapy is ensured by the adjustment of RTGT or TTGT according to the patient’s comfortable speed, actual need of body weight support, and his or her training intensity tolerance.

Participants in both groups will follow a two-week intensive conventional rehabilitation program with an add-on intervention (RTGT or TTGT) at the Rehabilitation Department of University Hospital Olomouc. The intensive conventional inpatient rehabilitation program will include individual physical therapy, which is based on neurophysiological approaches to improve movement patterns and is realized two times per day, with each session lasting for up to 45 min every weekday, and occupational therapy focused on improving abilities in activities of daily living, lasting for up to 45 min per day. Speech therapy or psychotherapy will be included if needed.

### 2.4. Blinding Procedure

All enrolled participants will be assessed by investigators that will be blinded to the group allocation. The physiotherapists performing the interventions (RTGT or TTGT) will not be blinded; however, they will not participate in the assessments at all and will not have any access to the interim and final results and outcomes. Although it is impossible to blind the participants due to the interventional study design, the participants will be instructed not to disclose their allocation to the investigators or the outcome assessors.

### 2.5. Study Protocol

All enrolled participants will be examined by evaluators that will be blinded to the group allocation. The assessments will be realized by certified neurologists, rehabilitation physicians, physiotherapists, and biomedical engineers with respect to their specialization at four assessment timepoints. Clinical visits will occur as follows:

Visit 0 (T0): enrolment 5–10 days after onset of qualifying IS at the Comprehensive Stroke Centre.

Visit 1 (T1) (3–5 days after V0): assessment before the initiation of an intensive rehabilitation program including assisted gait training (RTGT or TTGT) at the Department of Rehabilitation.

Visit 2 (T2) (14 ± 7 days after visit 1 and 1 month after visit 0): assessment at the end of the intensive rehabilitation program including gait training at the Department of Rehabilitation.

Visit 3 (T3): assessment 12 ± 1 weeks after visit 0 (3 months after visit 0).

Visit 4 (T4): assessment 24 ± 2 weeks after visit 0 (6 months after visit 0).

Scheduled outpatient visits in the GAITFAST trial will be performed by a neurologist at the Department of Neurology (visit 1–visit 4), a rehabilitation physician, a physiotherapist, and a biomedical engineer at the Kinesiology Laboratory at the Department of Rehabilitation (visit 1–visit 4). Multimodal MRI data will be acquired on a 3T scanner (Siemens Magnetom Vida, Erlangen, Germany) at the Department of Radiology. Scanning will be supervised by a member of the Functional Magnetic Resonance Imaging Laboratory (visit 1–visit 4). The duration of patient participation will be 6 months (Table 1).

Each visit will include an assessment to evaluate gait speed, gait dependency, neurological impairment, sensorimotor function, and gait biomechanics and a multimodal MRI of the brain. The outcome variables and study flow are presented in more detail in Table 2.

As data accumulate, the validity and the integrity of the trial will be subjected to an interim analysis after the first 30 participants have been assessed at all four assessment timepoints. With respect to the results of the interim analysis, the study design (such as the sample size, allocation ratio, or eligibility criteria) might be adaptively modified.

Adverse events (e.g., falls, pain, or dizziness) that occur during the study period, whether related to the study intervention or not, will be recorded. In case the training intervention is discontinued for any reason (e.g., hospital discharge, medical complications, or serious adverse event), a participant will not be required to participate in the follow-up assessments. Patients who suffer from a recurrent stroke during the study will be excluded, as will those with any medical condition or disease that occurs during the study and may affect limb movement or mobility. All enrolled patients may undergo outpatient rehabilitation after discharge from the Department of Rehabilitation. The types of rehabilitation treatment during follow-up will be recorded.

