### 2.7. Sample Size

Based on an analysis of our pilot data concerning the gait velocity (primary outcome), 120 participants (60 in each group) are anticipated to be enrolled in this study. This number of participants would provide 85% power (α level 5%) to detect a difference of 0.16 m/s in the 10 MWT (with respect to a missing data rate of 15% and an expected 10% drop in the follow-ups) between groups after intensive rehabilitation with add-on intervention. The gait speed difference of over 0.16 m/s was previously defined as the minimal clinically important difference in gait speed in subacute stroke patients [46].

For the multimodal magnetic resonance imaging (MRI), including functional MRI (fMRI), we have estimated that a sample size of 50 participants (25 in each group) will suffice to find significant correlations of MRI outcomes with gait recovery. This is based on previous studies of fMRI and gait recovery in similar clinical cohorts [29,32]. We will perform multimodal MRI in half of the randomly selected enrolled IS patients (1:2 randomization), i.e., in 60 participants, to allow for a common drop-out of examined patients with MR images of poor or insufficient quality. As we do not have sufficient information to estimate the variance in the outcomes, we plan to calculate the definitive effect sizes based on the interim analysis of the first 30 subjects measured within all four visits (visit 1–visit 4).

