As data accumulate, the validity and the integrity of the trial will be subjected to an interim analysis after the first 30 participants have been assessed at all four timepoints. The interim analysis, including the first 30 completely measured participants, will guide the final statistical methods. An interim analysis based on 30 participants with complete data will be conducted to perform a power analysis and to compute the final sample size. The principal investigator will have access to the interim results. Additional analyses and further subgroupings are not planned.

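### The 30-patient interim may change the design and the final analysis on its results, with no limit to blinded or variance-only data, so the 5% level is not guaranteed

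*Protocol article*

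**What the plan says.** Section 2.5 (Study Protocol) plans an interim analysis once 30 participants have been assessed at all four timepoints. Depending on its results, "the study design (such as the sample size, allocation ratio, or eligibility criteria) might be adaptively modified". The three items are given as examples, so the list is open.

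Section 2.10 (Statistical Analysis) adds three things:
- "The interim analysis, including the first 30 completely measured participants, will guide the final statistical methods".
- The interim serves to run a power analysis and to compute the final sample size.
- "The principal investigator will have access to the interim results".

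Section 2.7 (Sample Size) contains the only statement about the error level. It says that "120 participants (60 in each group) are anticipated to be enrolled in this study", giving "85% power (α level 5%) to detect a difference of 0.16 m/s in the 10 MWT", with allowance for 15% missing data and 10% loss to follow-up. No SD is given; the source is named only as pilot data.

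Section 2.4 (Blinding Procedure) bars the treating physiotherapists from interim results. It names no such bar for anyone else.

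**The concern.** A sample size re-estimate that uses only a nuisance parameter, such as the pooled SD, leaves the type I error almost untouched. The text describes something wider. The changes depend on the interim results, and the examples include the allocation ratio and eligibility, which a variance check would not normally lead anyone to alter. The final analysis method is also left to be guided by the same data. No rule, range or cap is stated for any change.

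Two things are at stake. First, if the new sample size depends on the observed difference between arms and the same patients are then counted in an ordinary 5% test, the true error rate depends on an unstated rule and can exceed 5%. Second, about 15 patients per arm give a very imprecise estimate of the difference, so a sample size built on it would be largely noise. Restricting the interim to completely measured patients also makes it a sample of completers.

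**Working it through.** **Inputs.** From section 2.7: difference 0.16 m/s, α 5% (taken as two-sided; sidedness is not stated), power 85%, 60 per arm, 15% missing, 10% loss. From sections 2.5 and 2.8: interim at 30 completers with 1:1 allocation, so about 15 per arm. Assumed: a normally distributed outcome and the floors and caps shown below.

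**1. The planned size.** The 120 cannot be reproduced without an SD, so I solve for it: SD = 0.16 × √(n/2) / (1.960 + 1.036).
- n = 60 per arm, no loss: 0.16 × 5.477 / 2.996 = 0.293 m/s.
- n = 60 × 0.85 × 0.90 = 45.9: 0.16 × 4.791 / 2.996 = 0.256 m/s.
- n = 60 × 0.75 = 45: 0.16 × 4.743 / 2.996 = 0.253 m/s.

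The planned size therefore implies an SD of about 0.25 to 0.29 m/s.

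**2. Precision at the interim.** The 95% confidence interval half-width is t(28) × SD × √(2/15), with t(28) = 2.048 and √(2/15) = 0.365.
- SD 0.25: 2.048 × 0.25 × 0.365 = 0.187 m/s.
- SD 0.29: 2.048 × 0.29 × 0.365 = 0.217 m/s.

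Both exceed the 0.16 m/s target. To see what this does to sizing, take SD 0.25 and a true difference of exactly 0.16. The standard error is 0.25 × 0.365 = 0.091. An estimate one standard error low (0.069) gives n = 2 × (2.996 × 0.25 / 0.069)² ≈ 238 per arm, up to rounding of 0.069. One standard error high (0.251) gives about 18. The value at 0.16 itself is about 44.

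**3. Type I error of an unadjusted final test.** Let z1 be the interim statistic (15 per arm) and z2 the independent statistic from later patients. Re-sizing for 85% power at the observed standardised effect |d| = |z1| × √(2/15) gives n = 2 × (2.996 / |d|)² = 134.7 / z1², clipped to a floor and a cap. The final statistic is Z = (√15 × z1 + √(n − 15) × z2) / √n, tested at ±1.96. Under the null, by simulation (2,000,000 runs for the fixed design and the floor-60 rows) and by numerical integration:

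| Per-arm n allowed | Two-sided type I error |
|---|---|
| Fixed at 60 | 5.0% |
| 60 to 120 | 5.6% |
| 60 to 240 | 5.9% to 6.0% |
| 16 to 200 | 7.3% |

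If n can only rise, even the choice of n most favourable to rejection at each z1 gives no more than 5.7% (cap 120) or 6.0% (cap 240).

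**4. Remedies under the same null.**
- Re-sizing on the arm-blind pooled SD: 4.8% (40,000 runs, Monte Carlo standard error 0.11 points).
- Re-sizing on the within-arm SD: 5.2%.
- Inverse-normal combination with weights fixed in advance, Z = √0.25 × z1 + √0.75 × z2 (15/60 = 0.25): 4.99%.

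**The case against.** The article says that the design might be modified, not that it will be. If nothing changes, or if only variance data are used, the level stays near 5%. It does not say outright that interim results are shown by arm, nor that the 30 are pooled into an unadjusted final test. A combination method, sizing rule and cap could sit in a full protocol or analysis plan that is not shown. This much stands: inflation is possible, not certain. It does not remove the point, because the article itself states open-ended, results-driven changes that reach the final methods.

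The larger error figure also needs a sharp cut in size. The interim waits for 30 patients to finish their 6-month visit, and recruitment may well continue meanwhile, so ending near 16 per arm is unlikely. The 5.6% to 6.0% range is the more realistic one.

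Several stronger readings are tempting but not supported:
- **Effect sizes.** Section 2.7 says "we plan to calculate the definitive effect sizes based on the interim analysis of the first 30 subjects". That sentence stands in the MRI paragraph and gives unknown variance as its reason, so it is no evidence about how gait speed will be re-sized.
- **An interim significance test, or a visit picked at the interim.** Neither is planned in the text.
- **Choice of test as a driver.** Choosing between a t test and a Mann–Whitney test by the smaller interim p-value gave 5.3%, against 5.0% to 5.2% for the two tests used without selection. This adds almost nothing.
- **Broken blinding.** The article does not make the principal investigator an outcome assessor, and aggregate results do not reveal individual allocations. Harm to the blinding of recruitment or assessment cannot be concluded.

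**Conclusion.** The point holds in a limited form. The documents allow interim results to alter sample size, allocation ratio or eligibility and to guide the final methods, without restricting the interim to blinded or variance-only data. The 5% level is therefore not guaranteed. A reader might infer that the final test has already ceased to be a 5% test; the text does not support that, because the outcome depends on a rule that is not stated.

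The likely size is modest: about 5.6% to 6.0% if the number per arm can only rise, and about 7.3% if it may also fall to 16 with a cap of 200. These figures assume a two-sided test, a normal outcome, 15 per arm at the interim, re-sizing on the observed effect and unadjusted pooling. The firmer conclusion concerns precision: for any SD consistent with the planned 120, the interim estimate is too imprecise to size the trial. Effects of a changed ratio or population were not quantified.

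**What to change.** Before the interim is run, amend sections 2.5, 2.7 and 2.10 as follows:
- Limit the interim to an arm-blind, pooled re-estimate of the gait-speed SD, using all available data and not completers only.
- Keep the target difference at 0.16 m/s. Allow the sample size only to be confirmed or raised, up to a cap stated in advance.
- Fix the final model beforehand and delete the sentence that lets the interim guide the final statistical methods.
- State that neither allocation ratio nor eligibility will change on between-arm results. Amendments on non-comparative grounds, such as feasibility, remain possible.
- Give the principal investigator only the resulting sample size.

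If a between-arm look is kept, specify an inverse-normal combination of the two stages with weights fixed in advance.

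The direct cost is protocol wording and a data file without arm labels. The team gives up redesign on early effect estimates, and the sample size may rise if the SD is larger than assumed. The arm-blind SD also absorbs part of any true difference: with SD 0.25 and a difference of 0.16, it becomes √(0.25² + 0.08²) = 0.262, which raises n by a factor of 0.0689 / 0.0625 = 1.10.
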